## Abstract

**Introduction::**

Malignant cutaneous epithelial tumors comprise various skin malignancies originating from the cutaneous epithelium, including cutaneous squamous cell carcinoma, basal cell carcinoma, and malignant cutaneous adnexal tumors. Treatment options are limited, as the rarity of these tumors, especially among Asians, renders well-controlled clinical trials extremely challenging to conduct. Thus, we designed a clinical trial to evaluate the efficacy and safety of the anti-programmed cell death-1 (PD-1) monoclonal antibody nivolumab in patients with metastatic cutaneous squamous cell carcinomas and other rare metastatic cutaneous epithelial tumors.

**Methods and analysis::**

This is an open-label, single-arm, multicenter, phase 2 clinical trial involving patients with metastatic malignant cutaneous epithelial tumors. Nivolumab (480 mg) will be administered intravenously every 4 weeks for a maximum of 26 doses. The primary outcome of the study will be the response rate based on response evaluation criteria in solid tumors, version 1.1. Assuming a null hypothesis of a response rate ≤5% and an alternative hypothesis of a 25% response rate, a minimum of 26 patients are required to achieve a 5% two-sided type I error and 80% power based on the exact binomial distribution. Finally, a target cohort size of 30 patients was determined as some patient dropout will be expected.

**Discussion::**

This is the first phase 2 clinical trial evaluating the efficacy and safety of the PD-1 inhibitor nivolumab in Asian patients with metastatic malignant cutaneous epithelial tumors. The findings of the study will contribute to the development of novel treatment approaches for patients with rare cutaneous malignancies, which remains an unmet clinical need.

**Trial registration::**

Registry number: jRCT 2031190048

## Introduction

1

Malignant cutaneous epithelial tumors, also referred to as non-melanoma skin cancer (NMSC), are common human neoplasms arising from the epidermis or cutaneous appendages. These include basal cell carcinoma (BCC), cutaneous squamous cell carcinoma (cSCC), extramammary Pagets disease (EMPD), and several other skin adnexal carcinomas. Of these, BCC and cSCC are the most common forms, accounting for 75% to 80% and 20% to 25% of all NMSC cases, respectively; other types of are extremely rare.^[1,2]^ The incidence of those varies, depending on the race, skin type, and geographic region, with a lower incidence in Asians compared with Caucasians. In general, NMSC has a favorable prognosis after local resection of the primary lesion. Reported rates of metastasis range between 0.0028% and 0.55% for BCC, while that for cSCC is 2.5%.^[3,4]^ Skin adnexal carcinomas are also considered to have a low metastatic potential.^[5]^ However, patients with metastatic disease have an extremely poor prognosis.^[6–8]^ The median overall survival (OS) of BCC patients is 10.0 months (range, 0.5–108.0 months),^[6]^ whereas those of cSCC and EMPD patients are 2.19 and 1.5 years, respectively.^[7,8]^

Treatment of those advanced forms have long been done by the administration of cytotoxic chemotherapeutic agents. Patients with cSCCs are often treated with bleomycin, peplomycin, irinotecan, platinum, anthracycline, taxanes, or 5-fluorouracil.^[9–16]^ For EMPDs, single-agent taxane, cisplatin, or fluoropyrimidine-based regimens are used.^[17–25]^ Nevertheless, evidence regarding the clinical benefit of these therapies is limited, mainly due to the rarity of these cancers and the challenges involved in the design of well-controlled clinical trials. Conducting clinical studies in patients with adnexal carcinomas is even more challenging, as the incidence of adnexal carcinoma is extremely low. The majority of commonly used cytotoxic agents have not gained regulatory approval for the treatment of metastatic malignant cutaneous epithelial tumors.

Increasing knowledge regarding cancer pathobiology, as well as advances in molecular biotechnology, have accelerated the development of targeted therapies. As for cSCC, the efficacy and safety of the monoclonal anti-epidermal growth factor receptor antibodies cetuximab and panitumumab and the orally administrated small-molecule inhibitors gefitinib and erlotinib have been reported.^[26–29]^ Orally administered small-molecule inhibitors of the Hedgehog signal pathway, vismodegib and sonidegib, have been approved by the U.S. Food and Drug Administration (FDA) for the treatment of advanced BCCs.^[30–33]^ The anti-epidermal growth factor receptor 2 (HER2) humanized monoclonal antibody trastuzumab was reported to provide a clinical benefit in patients with HER2-positive EMPD.^[34–37]^

Monoclonal antibodies targeting immune checkpoint molecules have emerged as promising therapeutic approaches for several human cancers. Particularly, monoclonal antibodies targeting programmed cell death 1 (PD-1) and its ligand, programmed cell death ligand 1 (PD-L1), have revolutionized the landscape of malignant skin cancer.^[38]^ The PD-1/-L1 pathway plays a critical role in tumor immune evasion across a broad range of tumor types. PD-1 is highly expressed in activated lymphocytes, whereas PD-L1 is expressed in cancer and stromal cells; binding of PD-L1 to PD-1 suppresses antitumor immune responses.^[39]^ Thus far, the FDA has approved the PD-1/PD-L1 inhibitors nivolumab and pembrolizumab for melanoma, cemiplimab for cSCC, and pembrolizumab and avelumab for Merkel cell carcinoma. However, no PD-1/PD-L1 inhibitors have been approved for use in cSCC patients in Japan. Furthermore, none of these agents are currently approved for rare adnexal tumors anywhere in the world.

To address these unmet medical needs, especially in Japanese patients with metastatic malignant cutaneous epithelial tumors, we designed a clinical trial to evaluate the efficacy and safety of nivolumab in Japanese patients with metastatic cSCC and other rare malignant cutaneous epithelial tumors.

## Methods/design

2

### Objectives, trial design, and study setting

2.1

This study is a single-arm, open-label, multi-institutional phase 2 clinical trial aiming to assess the efficacy and safety of nivolumab in patients with advanced malignant cutaneous epithelial tumors. The recruitment of study participants started in July 2019 and will continue until a total of 30 participants are registered. The study will be conducted in 8 centers: Keio University Hospital, Tohoku University Hospital, Niigata Cancer Center Hospital, National Cancer Center Hospital, Nagoya University Hospital, Kyoto University Hospital, Wakayama Medical University Hospital, and National Hospital Organization Kyushu Cancer Center. All study participants are required to sign an informed consent form by the investigators. Nivolumab will be administrated every 4 weeks for up to 26 cycles; the treatment will continue for up to 2 years in patients benefiting from the treatment who show no evidence of disease progression.

### Eligibility criteria

2.2

#### Inclusion criteria

2.2.1

1.Age: 20 years or older.2.Histologically confirmed incurable, advanced, or recurrent epithelial skin malignancies after surgical treatment and/or radiotherapy.3.≥1 measurable lesions based on RECIST 1.14.ECOG performance status 0-1.5.Life expectancy ≥90 days6.Women willing to use double contraception and agree not to breastfeed for at least 5 months after final administration.Men willing to use double contraception for at least 5 months after final administration.7.Sufficient organ functions: all of the following conditions are fulfilled:White blood cell ≥2000/mm^3^Absolute neutrophil count ≥1500/mm^3^Platelets ≥100,000/mm^3^Hemoglobin ≥9.0 g/dlAST and ALT ≤ 3times the upper limit of normalTotal bilirubin ≤ 2 times the upper limit of normalSerum creatinine ≤ 1.5 mg/dl or creatinine clearance or eGFR ≥ 45 ml/minute.

Patients received an adequate explanation about the study and provided informed consent.

#### Exclusion criteria

2.2.2

1.History of anaphylaxis to other antibody formulations, severe allergy, chronic or recurrent autoimmune disease, transplantation therapy, recent transient cerebral ischemic attack or cerebral vascular accident, recent thrombosis, or thromboembolism.2.History of additional malignancy except for completely resected BCC, carcinoma *in situ*, intramucosal cancer, superficial bladder cancer, or other cancers that have not recurred for at least 5 years before enrollment.3.History of pretreatment using anti-PD1/L1/L2, anti-CD137, anti-CTLA-4 inhibitor or any other antibody or drugs intended for T-cell regulation.4.Active central nervous system (CNS) metastases5.Uncontrolled tumor-associated pain6.Current disease; active autoimmune disease, diverticulitis or symptomatic peptic ulcer disease, pericardial effusion, pleural effusion or ascites requiring sustained treatment, uncontrollable diabetes mellitus, systemic infection requiring treatment, interstitial lung diseases, pulmonary fibrosis, or unstabled radiation pneumonitis, uncontrollable or severe cardiovascular disease.7.Recent following treatments within 28 days prior to the enrollment; systemic adrenocortical hormone, immunosuppressant, unapproved drugs, any antineoplastic agent, surgical adhesion of the pleura or pericardium, surgery under general anesthesia, radiotherapy.8.Received surgery under local or topical anesthesia within 14 days prior to the enrollment.9.Received any radiopharmaceuticals within 56 days prior to the enrolment.10.Seropositive for HBsAg, HCV-Ab, or HIV-Ab.11.Pregnant, breast-feeding or potentially pregnant.12.History of any condition or therapy that might confound the results of this study.

#### Ethics approval and consent to participate

2.2.3

This study is being conducted in accordance with the principles expressed in the Declaration of Helsinki, good clinical practice guidelines and SPIRIT (Standard Protocol Items: Recommendations for Interventional Trials) guidelines. The protocol version 1.0 was approved by the Institutional Review Board of Keio University Hospital in May 2019 and the institutional review board of the following participating center: Tohoku University Hospital, Niigata Cancer Center Hospital, National Cancer Center Hospital, Nagoya University Hospital, Kyoto University Hospital, Wakayama Medical University Hospital, and National Hospital Organization Kyushu Cancer Center. Written informed consent has been obtained from all enrolled participants.

#### Endpoints

2.2.4

The primary outcome of this study will be the response rate based on RECIST, version 1.1 criteria. Secondary outcome measures include the best overall response rate, progression-free survival (PFS), OS, disease control rate, and adverse events graded using the National Cancer Institute Common Terminology Criteria for Adverse Events, version 4.0. For this study, PFS will be defined as the time from initiation of treatment in the clinical trial to disease progression or death from any cause, and OS will be defined as the time from initiation of treatment in the clinical trial to death from any cause. The response rate based on the immune RECIST will also be assessed as an exploratory outcome measure.

#### Treatment methods

2.2.5

The trial schedule is composed of 3 periods the screening, treatment, and post-observation periods. The screening period starts from the date of consent acquisition to the day before the first administration of the study drug. During this screening period, inclusion/exclusion criteria for the study participants will be evaluated. During the treatment period, 480 mg nivolumab will be administered intravenously over 30 minutes, every 4 weeks. Administration of the study drug will be continued for up to 26 doses, with a maximum treatment period of 2 years. Study participants will be assessed for a tumor response every 2 treatment cycles by imaging. Any patients who meet the criteria for discontinuation of the treatment or who have completed the 2-year administration period will be assessed for a tumor response and move into the post-observation period. During the post-observation period, adverse events will be reported 28 days after the last dose of nivolumab. Subsequently, tumor lesions will be monitored every 8 weeks by imaging during the follow-up period. To determine OS, all subjects will be followed-up until death, withdrawal of consent, or the end of the study.

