#### Criteria for discontinuation of the treatment

2.2.6

The administration of nivolumab will be discontinued in patients who experience at least 1 of the following:

1.a radiographic complete response according to the response evaluation criteria in solid tumors (RECIST) version 1.1, with the exception of cases with a high risk of recurrence;2.radiographic disease progression according to the RECIST, version 1.1 or apparent disease progression with clinical symptoms;3.grade 3 or higher interstitial pneumonia;4.grade 2 or higher eye pain or blurred vision, regarded as a response to the study drug, showing no improvement to ≤ grade 1 after appropriate treatment;5.grade 3 or higher bronchospasm, diarrhea, colitis, neurotoxicity, hypersensitive reaction, infusion reaction, or uveitis, regarded as a response to the study drug;6.grade 3 or higher thrombocytopenia for ≥5 days;7.more than 10 weeks from the start of the previous treatment cycle;8.the investigator or physician decides to discontinue administration of the drug.

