#### Sample size calculation

2.2.9

Assuming a null hypothesis of a response rate of ≤5% and an alternative hypothesis of 25%, a minimum of 26 patients are required to achieve a 5% two-sided type I error and 80% power based on the exact binomial distribution. A target sample size of 30 was set to account for an expected patient dropout of 10%.

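### On-treatment scans follow treatment cycles rather than the calendar, so dose delays can stretch the scan interval from 8 to 14 weeks, or 20 at the extreme, and could modestly inflate recorded PFS

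*Protocol article*

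**What the plan says.** All statements are in the protocol article.

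- **Dosing** (Treatment methods): "480 mg nivolumab will be administered intravenously over 30 minutes, every 4 weeks".
- **Imaging on treatment** (same section): "Study participants will be assessed for a tumor response every 2 treatment cycles by imaging". No calendar interval is given.
- **Imaging after treatment** (same section): "tumor lesions will be monitored every 8 weeks by imaging during the follow-up period". A tumor assessment is also made when a patient stops or completes treatment.
- **Longest tolerated delay** (Criteria for discontinuation of the treatment, item 7): treatment ends at "more than 10 weeks from the start of the previous treatment cycle". Up to that limit, a late patient remains on treatment.
- **Clinical progression** (same section, item 2): "apparent disease progression with clinical symptoms" is also a reason to stop, which leads to the assessment at discontinuation.
- **Endpoint** (Endpoints): PFS is secondary. "PFS will be defined as the time from initiation of treatment in the clinical trial to disease progression or death from any cause".

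**The concern.** One endpoint is observed on two clocks. On treatment the clock is the cycle count; afterwards it is the calendar. The two agree only when every dose is on time, and the 10-week rule shows that late doses are foreseen.

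Progression seen only on imaging cannot be recorded before it happens; it is recorded at the next scan. A longer gap therefore moves the recorded date later on average. Where toxicity causes the delay, how often a patient is assessed depends on how that patient tolerates the drug. The first opportunity to record a response moves as well.

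The trial has a single arm, so no control group shares the distortion. Whatever its size, it passes into the absolute PFS estimate and into any comparison with outside data.

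**Working it through.** **The plan's own figures.** The article gives no PFS figure. Its only design calculation is the sample size, and it reproduces: at n = 26, with null rate 5%, alternative 25% and an exact upper tail of at most 0.025, at least 5 responses are needed, the attained one-sided error is 0.0085 and the power is 0.816. Scan timing is not an input to that calculation.

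**Step 1: scheduled scan interval** (sum of two consecutive cycle lengths; 4 weeks nominal, 10 weeks the longest before discontinuation)

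- No delay: 4 + 4 = 8 weeks, equal to the follow-up interval.
- One maximal delay: 4 + 10 = 14 weeks.
- Two maximal delays in a row: 10 + 10 = 20 weeks.

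**Step 2: mean lag from true to recorded progression in a patient scanned every L weeks.** Assume exponential progression times with rate λ = ln 2 / median, and progression recorded at the next scheduled scan. Then

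mean lag = L / (1 − exp(−λL)) − 1/λ.

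The article gives no median PFS, so I take 13 to 52 weeks. Example with median 13 weeks and L = 8: λ = 0.0533, 1/λ = 18.76, 8 / 0.3472 = 23.04, so the lag is 4.3 weeks.

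| L (weeks) | Mean lag, medians 52 to 13 weeks |
|---|---|
| 8 | 4.1 to 4.3 weeks |
| 14 | 7.2 to 7.9 weeks |
| 20 | 10.4 to 11.7 weeks |

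An 8-week schedule already carries a lag of about 4 weeks. The issue is the excess over that: roughly 3 to 3.6 weeks at L = 14, and 6 to 7.5 weeks at L = 20.

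**Step 3: effect on the whole cohort.** The share of patients delayed is not given either, so I take 10% to 50%, with median PFS of 17.3 or 26 weeks. Two patterns are compared with fixed 8-week scans: one stretched interval per delayed patient (starting at week 0, 8 or 16, equally likely), or every interval stretched to 14 or 20 weeks.

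- Rise in mean recorded PFS: about 0.1 to 1.5 weeks with one stretched interval; 0.3 to 3.6 weeks with all stretched.
- Rise in the 26-week PFS rate: about 0.6 to 9 points across all these scenarios.
- Median: unchanged in nearly every scenario, because it sits on the scan grid. It moved only with half the patients delayed, and then in either direction (24 to 22 or 20 weeks; 32 to 30 or 40 weeks).

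**Worked example** (median 17.3 weeks, so λ = 0.0401; 20% of patients with one 20-week interval). With 8-week scans, a patient is recorded as progression-free at week 26 if still so at the week-24 scan: exp(−24λ) = 38.2%. If the long interval starts at week 0, 8 or 16, the last scan before week 26 is at week 20, 8 or 16, giving 44.9%, 72.6% and 52.7%, with mean 56.7%. The cohort rate is 0.8 × 38.2% + 0.2 × 56.7% = 41.9% (41.8% by simulation), a rise of 3.7 points.

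**Step 4: comparison with sampling error.** With 30 patients and a rate near 38%, the standard error is √(0.382 × 0.618 / 30) = 8.9 points, or about ±17 points for a 95% interval.

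**The case against.** **Condensed source.** The article summarises a fuller protocol, which may set scan windows, and it does not say in terms that a late dose postpones the scan. Its nominal on-treatment and follow-up intervals are both 8 weeks, so it does not contradict itself. This stands in part: a missing window would be no finding. But the article itself states the anchor, and a window placed around a cycle-based visit does not remove the dependence on delays.

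**The 20-week figure is an extreme.** This stands. It needs two maximal delays in a row. The exposed group is also narrowed, because several listed toxicities (items 3, 5 and 6 of the discontinuation criteria) lead to stopping rather than waiting, and stopping brings a tumor assessment followed by 8-weekly scans.

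**Progression is not found only at scheduled scans.** This stands too. Deaths count as PFS events whatever the scan dates, and clinically apparent progression ends treatment and prompts an assessment. The lags in the working are therefore upper figures for patients delayed that far.

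**Low consequence.** PFS is secondary, and the article states no PFS threshold, hypothesis or comparator. The worked shift of 3.7 points is well inside sampling error. That limits the weight of the point, but sampling error is random, whereas this shift in mean and landmark PFS has a direction.

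**Stronger readings.** A reader might infer that the trial's PFS is biased upward by many weeks, or that the on-treatment and follow-up parts of the curve cannot be compared. The documents support neither. They give no delay frequency, the median usually stays put, and patients who stop for progression have already had their event and add nothing to the follow-up part.

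**Conclusion.** The point holds in limited form. As written, the on-treatment scan interval depends on dose delays: 8 weeks without delay, 14 with one maximal delay, and 20 in the extreme. If delays are common, mean and landmark PFS can be modestly inflated and response timing shifted. The median usually does not change.

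The intervals follow directly from the article. The PFS effects in weeks and points do not: they rest on exponential progression times, assumed medians of 17.3 or 26 weeks, an assumed 10% to 50% of patients delayed, and progression detected only at scheduled scans. The last of these overstates the effect. A conclusion that PFS is materially biased would need delay data that the article does not contain.

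The primary response-rate test is not materially affected, because it counts responders rather than timing them. The point is worth correcting because the correction is cheap, not because the trial's main conclusion is at risk.

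**What to change.** In Treatment methods, schedule on-treatment tumor imaging every 8 weeks counted from first dose, regardless of dose delays, with a stated window (for example plus or minus 1 week). This matches the interval already used in follow-up and the one already implied for undelayed patients. No dosing or discontinuation rule changes.

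With the fix, the mean lag stays at about 4.1 to 4.3 weeks for every patient under the assumptions above.

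The cost is a minor amendment, to be put through at eight centers, and a few scans outside dosing visits in delayed patients. Patients on schedule are unaffected. Recruitment began in July 2019 and was expected to finish in early 2021, so a late change would leave two imaging schedules within about 30 patients. If it comes too late for patients already enrolled, report PFS with an interval-censored sensitivity analysis using the actual scan dates. That analysis would reflect the wider uncertainty from long gaps, but it cannot replace scans that were not done.

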#### Criteria for discontinuation of the treatment

2.2.6

The administration of nivolumab will be discontinued in patients who experience at least 1 of the following:

1.a radiographic complete response according to the response evaluation criteria in solid tumors (RECIST) version 1.1, with the exception of cases with a high risk of recurrence;2.radiographic disease progression according to the RECIST, version 1.1 or apparent disease progression with clinical symptoms;3.grade 3 or higher interstitial pneumonia;4.grade 2 or higher eye pain or blurred vision, regarded as a response to the study drug, showing no improvement to ≤ grade 1 after appropriate treatment;5.grade 3 or higher bronchospasm, diarrhea, colitis, neurotoxicity, hypersensitive reaction, infusion reaction, or uveitis, regarded as a response to the study drug;6.grade 3 or higher thrombocytopenia for ≥5 days;7.more than 10 weeks from the start of the previous treatment cycle;8.the investigator or physician decides to discontinue administration of the drug.

#### Concomitant medications

2.2.7

Medications specifically prohibited in the exclusion criteria will be not allowed during the ongoing trial. Patients are also prohibited from receiving the following therapies during the screening and treatment phase of the study:

Any investigational medication other than the study drug.Any anticancer therapies including chemotherapy or biologic therapy other than the study medication, excluding the follows:Intravenous infusion of zoledronic acid hydrate, pamidronate disodium or subcutaneous injection of denosumab, started for bone metastases before enrollment in this study

Systemic steroid therapy can be combined when immune-related adverse events caused by the study drug are suspected.

